### Rationale and objective

1.5

#### Primary objective

1.5.1

Our **primary objective** is to determine whether the use of a pedometer and an activity book incorporating strategies of self‐monitoring and goal setting can help in‐patients with major depression to increase steps and to further decrease depression in comparison to TAU.

#### Secondary objectives

1.5.2

**Most important secondary objectives** are to compare changes in subjective PA, objective PA, anxiety severity as well as in the duration of in‐patient treatment between PI and TAU.

Further **secondary objectives** are to determine if the PI group differs from TAU group from baseline (first to third day of inpatient treatment) to end of inpatient treatment (three days before end of inpatient treatment) in

psychopathological symptomshealth‐related quality of lifeself‐reported depressive symptomsPA: self‐efficacy, intention, self‐concordance of goal‐striving, outcome expectations, planning, and barrier planninggeneral self‐efficacy

#### Research hypotheses

1.5.3

Hypotheses of this trial are:

From hospital admission to the end of inpatient treatment patients of the PI group in contrast to the TAU group show:

Increased PA and decreased depressionDecreased anxiety and duration of hospital treatment

## METHOD

2

### Study design

2.1

We use two treatment arms in a longitudinal randomized single‐blinded (rater)controlled parallel group design with points of measurement at Day 1–3 after hospital admission (baseline, T0), after 4 weeks (T1a), at discharge (T1b), and 6 months after hospital admission (follow‐up, T2; see Figure 1).

**FIGURE 1 mpr1862-fig-0001:**
[figure not shown]
Flowchart of the SAD study. PI, pedometer intervention; SAD, Step Away from Depression; TAU, treatment as usual

### Study setting

2.2

Selection of these clinics is done due to collaboration in the “Referat für Sportpsychiatrie und –psychotherapie” of the DGPPN including universitary as well as municipal psychiatric clinics in urban and rural areas.

### Participants and eligibility

2.3

#### Inclusion criteria

2.3.1

Inpatients are eligible to the trial if they

have unipolar major depression as primary diagnosisare aged from 18 to 65 yearshave a prospected inpatient treatment of at least 4 weeksare able to understand German language andcan be recruited within the first three days after hospital admission

#### Exclusion criteria

2.3.2

Exclusion diagnoses are psychotic depression, borderline personality disorder, schizophrenia, anorexia nervosa, and dementia. Furthermore, we exclude patients with current substance addiction (besides nicotine), acute suicidality, pregnancy, regular use of pedometers, and patients with medical disorders resulting in the inability to walk with mild to moderate intensity at least 5000 steps per day or physical, laboratory, or electrocardiography findings that would put patients at risk if they increase their daily steps. Patients with more than 10,000 steps at baseline are equally excluded from the study.

### Randomization and treatment conditions

2.4

#### Randomization

2.4.1

Patients are randomly allocated into one of two groups: (1) TAU or (2) TAU plus PI. Randomization—done by a computerized random number generator—is stratified by center with an intended allocation ratio of 1:1. Group assignment is implemented via sequentially numbered, sealed, opaque envelopes. Group allocation is disclosed after baseline measurement.

#### Treatment as usual

2.4.2

TAU, the control condition, comprises inpatient clinical treatment with psychotherapy in group and/or individual settings as well as pharmacotherapy and other adjuvant treatments like sociotherapy, occupational therapy, music therapy, physiotherapy. Most clinics also offer PA interventions such as exercise therapy or yoga. Concomitant care is not restrained in both groups during and after inpatient treatment. Patients in the TAU condition do not receive a pedometer or diary.

#### Pedometer intervention

2.4.3

Patients in PI group receive an Omron Walking style IV pedometer (Model HJ‐325‐EW)—a small tool, fixed at the belt or worn in the pockets that records number of steps. Additionally, we provide patients with an activity book. Instruction is to fill in daily steps as displayed by the pedometers. Furthermore, patients should increase the daily step goal by 500 steps compared to their former base level (see Figure 2). Pedometers are blinded by masking their display with adhesive tape for baseline measurement. The average step number of these three days serves as starting value for the intervention. By the beginning of the PI pedometers are unblinded. If patients achieve the new goal for at least 4 of 7 weekdays, they should continue increasing the number of steps for the next week. If they do not reach their goal, they should keep this goal again for the coming week. When 10,000 steps per day are attained, patients can individually decide whether to further increase the level or to continue with 10,000 steps. To sum up, PI consists of (1) daily wearing of the pedometer, (2) recording steps in the activity diary, and (3) weekly raising number of steps by 500 or maintaining 10,000 daily steps, during the whole inpatient‐stay and afterward for a total of 26 weeks.

**FIGURE 2 mpr1862-fig-0002:**
[figure not shown]
Example of “Week 2” of the activity diary

### Procedure and recruitment

2.5

Trial staff members in different centers are psychiatrists, clinical psychologists, and/or advanced students of psychology or medicine. All staff members are trained with standard material and instructions. Main task of the staff is to carry out measurements in a uniform reproducible manner and to give predefined instructions to the PI group how to use the pedometer and the activity diary. Participants fill out questionnaires online via SoSci‐Survey (Leiner, 2019) under www.soscisurvey.de or, if not possible (due to technical restrictions of the clinic or personal preferences of the patient), by paper–pencil.

Recruitment takes place at hospital admission or up to 3 working days after. Eligibility of patients is checked systematically for every patient newly admitted to the ward. The study personnel contacts eligible patients, delivers information sheets about the study and gives opportunity to discuss any belonging issue. In case of acceptance, patients give their written informed consent. Trial staff members then arrange all measurement appointments with patients throughout the study.

To promote retention, patients receive reimbursement of 15 Euro only if they attend the Follow‐Up‐Measurement. Patients are not controlled how they follow the PI or how pedometer data is recorded in the diary. In order to monitor adherence of the PI group to the intervention, study personnel makes copies of the activity diary at T1‐ and T2‐Measurement. PI participants are allowed to keep their pedometer for personal use after participation in the study, independently of adherence or dropout.

### Data collection

2.6

Table 1 displays all measurements at different points in time line. All questionnaires are administered in German language.

**TABLE 1 mpr1862-tbl-0001:** Time table of measurements

		T0 (baseline)	T1a (4 weeks)	T1b (discharge)	T2 (follow‐up)
Physical activity					
Objective	Accelerometer measurement for 3 days (primary outcome)	x	x	x	x
Subjective	**Q:** IPAQ short version (7)	x	x	x	x
Adherence	**AD:** Copy of step protocols (IG only)	‐	x	x	x
Depression					
Objective	**I:** Montgomery–Åsberg Depression Rating Scale (primary outcome) (10)	x	x	x	x
Subjective	**Q:** Beck‐Depression‐Inventory II (21)	x	x	x	x
General, physical, and clinical measures					
General measures	**Q:** Sociodemographic data, medication	x	‐	‐	‐
Physiological measures	**HR:** Blood pressure, heart rate, weight, and blood glucose	x	‐	‐	‐
Laboratory values	**HR:** Triglycerides, cholesterol, high density lipoprotein, low density lipoprotein	x	‐	‐	‐
Clinical history	**Q:** Anamnestic questions (6)	x	‐	‐	‐
Psychiatric symptoms	**Q:** Symptom checklist 27 (27)	x	x	x	x
Anxiety	**Q:** Beck anxiety inventory (21)	x	x	x	x
General health quality	**Q:** Short‐Form Health‐Survey 12 (12)	x	x	x	x
Intervention evaluation	**Q:** Questions about the implementation of PI (5)	‐	‐	‐	x
Treatment history	**Q:** Concomitant treatment since discharge (13)	‐	‐	‐	x
Critical life events	**Q:** Social Readjustment Rating Scale (43)	‐	‐	‐	x
Components of the MoVo‐model					
Intention, motivation and volition	**Q:** Intention (2), physical activity specific self‐efficacy (6), outcome expectancies (6), self‐concordance scale (12), action planning (4), coping planning (4)	x	x	x	x

Abbreviations: ( ), number of items; AD, activity diary; HR, information out of hospital record; I, interview; IPAQ, International Physical Activity Questionnaire; MoVo‐Model, Motivation Volition Process Model; PI, pedometer intervention; Q, Online‐Questionnaire or Paper/Pencil.

### Primary outcome measures

2.7

#### PA—Objective

2.7.1

To objectively measure steps and overall PA we use ActiGraph GT1M accelerometers (ActiGraph). The GT1M counts the incidences of change in acceleration per minute and can therefore measure the amount of PA. Additionally, it measures steps. Accelerometers have already been used in former research and proved being a reliable instrument for measuring PA (Kaminsky & Ozemek, 2012; Silva, Mota, Esliger, & Welk, 2010), also for samples with patients with mental disorders (Petzold et al., 2017). For different activity levels, we set thresholds according to the ActiLife Software (ActiLife 6 User's Manual, 2008): light (≤1952 counts per minute), moderate (1953–5724 counts per minute), hard (5725–9498 counts per minute), and very hard (≥9499 counts per minute). For measuring the activity of less active people, two to three valid days of wearing the accelerometer are enough for sufficiently valid data (Kocherginsky, Huisingh‐Scheetz, Dale, Lauderdale, & Waite, 2017). Therefore, patients are instructed to carry the accelerometer around their hip for 3 consecutive days while being awake. Mean step count is used as summary measure format.

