**Methods:**

The Step Away from Depression (SAD) study is a multicenter randomized controlled trial targeting 400 patients with major depressive disorder. Treatment as usual (TAU) is compared to TAU plus PI after 4 weeks, at discharge, and 6 months after hospital admission. Primary outcomes are clinically rated depression severity and accelerometer‐measured step counts. Secondary outcomes include self‐reported depression symptoms and PA level, psychiatric symptoms, health‐related quality of life, self‐efficacy, and components of the Motivation Volition Process Model.

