### Daily amount of PA in healthy people and in patients with depression

1.2

The World Health Organization (WHO) proposes an amount of 150 min of moderate activity or 75 min of vigorous activity per week or any corresponding combination of these two (World Health Organization, 2010). Moreover, this activity should be executed in time bouts of at least 10 min 63.2% of the overall population of high‐income Western countries comply with these PA sufficiency recommendations (Guthold, Stevens, Riley, & Bull, 2018). Reaching the goal of 10,000 steps per day is still a popular goal in pedometer use (Tudor‐Locke et al., 2011) Healthy people aged 18–65 years usually walk 9797 steps per day (Bohannon, 2007). However, especially concerning low active persons, raising the amount of steps gradually and regularly seems to be more important for health benefit than reaching the goal of 10,000 steps per day (Hallam, Bilsborough, & de Courten, 2018; Lee et al., 2019). Of people with mental disorders, 41.7% fulfill the criteria of the American College of Sports Medicine for PA (30 min of moderate activity on 5 days or 20 min of vigorous activity on three days or 1000 MET minutes in 1 week; Petzold et al., 2017). The percentage of people with depression with insufficient PA seems to be roughly twice as high as that of healthy individuals. Around two thirds (67.8 %) of depressive patients report insufficient PA (F. Schuch et al., 2017). Overall, literature shows that PA self‐report data likely overestimates objective PA (Chaudhury, Stamatakis, Roth, & Mindell, 2010; Garriguet, Tremblay, & Colley, 2015). When only objective measures of PA are taken into account, the percentage of insufficiently active depressive patients even increases up to 85.7. In summary, the figures are alarming and call for interventions to increase daily life PA, even more for people with depressive disorders.

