#### PA—Subjective

2.8.1

Self‐reports of PA are assessed with the International Physical Activity Questionnaire (IPAQ; Craig et al., 2003). We use the short “last 7 days” self‐administered version measuring time spent with four activity levels (vigorous activity, moderate activity, walking, and sitting). The IPAQ correlates moderately with accelerometer data in samples with mental disorders (overall PA: *r* = 0.47; Petzold et al., 2017).

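### As printed, the accelerometer's light level has no lower bound, so minutes in that level include worn sitting time and follow wear time (minor; secondary time-in-level results only)

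*Protocol article*

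**What the plan says.** Section 2.7.1 (PA—Objective) uses a hip-worn accelerometer for steps and for overall physical activity. It introduces the intensity levels with "For different activity levels, we set thresholds according to the ActiLife Software" and lists them as "light (≤1952 counts per minute), moderate (1953–5724 counts per minute), hard (5725–9498 counts per minute), and very hard (≥9499 counts per minute". No sedentary or inactive level appears.

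The same section says of the device "Additionally, it measures steps", and closes with "Mean step count is used as summary measure format". The abstract gives accelerometer-"measured step counts" as one of the two primary outcomes.

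Section 1.5.2 (Secondary objectives) describes the leading secondary aims in these words: "are to compare changes in subjective PA, objective PA, anxiety severity as well as in the duration of in‐patient treatment between PI and TAU". It does not say which accelerometer measure stands for objective PA.

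Section 2.9.2 (Statistical analyses) requires at least eight hours of wear per day and two complete days for a valid measurement. Section 4 (Discussion) acknowledges that the trial has no control over wear time.

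**The concern.** A level called light activity should separate some movement from none. As printed it does not, because zero counts satisfy the rule. Two consequences follow for any table of minutes by level.

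- Light minutes rise when the device is worn longer, even if the extra time is spent sitting. Only raters are blinded (section 2.1), so patients know their arm and wear could differ between arms. The eight-hour rule sets a minimum and does not equalise wear.
- Light minutes do not move when sitting is replaced by walking below 1953 counts per minute. The pedometer intervention sets step goals with no intensity target (section 2.4.3), so some of the added walking may fall in that range.

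At stake is a secondary result that could be misread: more light activity in an arm that only wore the device longer, or no change in an arm that sat less and walked slowly more.

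**Working it through.** **Inputs from the article.** The four count bands (section 2.7.1) and the minimum valid day of 8 h = 480 min (section 2.9.2).

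**Assumptions, not in the article.** 30 min per day at moderate or above; sitting at 0 counts per minute; slow walking below 1953 counts but above whatever sedentary cut-point is chosen; 100 steps per minute when walking (range 60–120).

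**Step 1: the bands as printed.** Each band starts one count above the end of the one before (1952/1953, 5724/5725, 9498/9499), so every value is classified. Values of 0, 50, 100, 500, 1500 and 1952 counts per minute all fall in light; 1953 is the first in moderate.

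**Step 2: the identity.** The bands cover every worn minute, so

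light minutes = wear minutes − minutes at moderate or above.

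Sitting time does not enter. A patient who sits through the whole 480-minute day scores 480 − 0 = 480 light minutes.

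**Step 3: four illustrative days.**

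| Day | Sitting | Slow walking | Moderate or above | Wear | Light as printed | Light share as printed |
|---|---|---|---|---|---|---|
| A: mostly sitting | 430 | 20 | 30 | 480 | 480 − 30 = 450 | 93.8% |
| B: much less sitting | 250 | 200 | 30 | 480 | 480 − 30 = 450 | 93.8% |
| C: A with 20 min moved from sitting to slow walking | 410 | 40 | 30 | 480 | 480 − 30 = 450 | 93.8% |
| D: A plus 60 min worn while sitting | 490 | 20 | 30 | 540 | 540 − 30 = 510 | 94.4% |

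Days A, B and C cannot be told apart. Day D shows 60 more light minutes with no added movement. Dividing by wear time removes most of the wear effect (93.8% against 94.4%) but leaves A, B and C identical, so shares alone are not enough.

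**Step 4: the same days with the lowest level split.**

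| Day | Sedentary share | Light share | Moderate-or-above share |
|---|---|---|---|
| A | 430/480 = 89.6% | 20/480 = 4.2% | 30/480 = 6.3% |
| B | 250/480 = 52.1% | 200/480 = 41.7% | 30/480 = 6.3% |
| C | 410/480 = 85.4% | 40/480 = 8.3% | 30/480 = 6.3% |
| D | 490/540 = 90.7% | 20/540 = 3.7% | 30/540 = 5.6% |

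The shift from A to C is now visible, and longer sedentary wear no longer appears as extra light activity.

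**Step 5: what the step count does.** The 20 minutes of walking added in day C give 20 × 100 = 2000 steps (20 × 60 = 1200 to 20 × 120 = 2400). The mean step count therefore registers the change that the levels miss. If the added walking reached 1953 counts or more, the levels would register it too: light would fall by 20 minutes and moderate would rise by 20.

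**Step 6: what is untouched.** The stated sample size reproduces without any count band. With two groups, two outcomes, f² = 0.06, a 5% level and noncentrality N × f², the smallest N for 95% power is 261, and power at 262 is 0.951. The WHO recommendation is described in section 1.2 by moderate and vigorous activity, so a floor under light does not affect that benchmark.

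**The case against.** The strongest reply is that little depends on the light level. Mean step count is the stated summary measure and a primary outcome, and the intervention is defined by steps. The article's own rationale is also about steps: "especially concerning low active persons, raising the amount of steps gradually and regularly seems to be more important for health benefit". No section announces a comparison of light minutes between arms, and secondary results are labelled exploratory. The thresholds are taken from a software manual that is not at hand and may contain a sedentary setting. The article may also condense a fuller plan.

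Most of this stands, and it rules out three stronger readings that a reader might infer.

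- *That the trial cannot see a shift from sitting to slow walking.* Not supported: the step count sees it (step 5), and the self-report questionnaire records walking and sitting as well.
- *That the secondary objective on objective PA cannot be answered.* Not supported: section 1.5.2 does not define that objective as time in level, and nothing there excludes steps.
- *That the objective and subjective measures are mismatched because the questionnaire works by "measuring time spent with four activity levels (vigorous activity, moderate activity, walking, and sitting".* Not supported as a defect: nothing promises matching levels, and those categories mix type of activity with intensity.

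The reply does not remove the scoring rule. The article does not leave the thresholds to another document; it prints them, and as printed they score stillness as light activity. Objective PA is also listed as a secondary objective although steps are already primary. If time in level is reported under that objective, this is the rule that would produce it.

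**Conclusion.** The point holds in a narrow form and is minor. As printed, light minutes are wear time minus moderate-and-above time. They rise one for one with sedentary wear and change by 0 when sitting gives way to walking below 1953 counts. That much follows from the printed bands alone.

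The practical size is not known. The 30, 20 and 60 minutes above are illustrations. The article does not say how much intervention walking falls below 1953 counts, or whether wear differs between arms. Whether the cited manual defines a sedentary level could not be checked.

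Only time-in-level results reported for the secondary objective on objective PA are affected.

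**What to change.** Before analysis, split the lowest level into sedentary and light at a cut-point that has a cited source and is fixed in advance. Report sedentary, light and moderate-or-above time as shares of wear time, by arm. The split and the shares are both needed, for the reason shown in step 3.

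If the split is not made, state that the light level includes sedentary time, and neither interpret light minutes as activity nor compare them between arms.

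The first option costs one more cut-point to justify and a re-scoring of the existing accelerometer files (assuming they are stored), with no new data. The second costs a sentence. Neither changes the primary outcomes, the MANOVA or the sample size.

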#### Depression—Objective

2.7.2

For objective rating we use the Montgomery–Åsberg Depression Rating Scale (MADRS; Montgomery & Asberg, 1979). Scores of 10 or less on the MADRS are considered to indicate remission (Hawley, Gale, & Sivakumaran, 2002; Zimmerman, Posternak, & Chelminski, 2004) and a decrease of 50% of symptoms as response. MADRS assessments are performed by blinded staff personnel. Raters are trained to ensure interrater reliability. Interrater correlations of these trainings show a Cronbach's Alpha of 0.978 (CI: 0.95–0.99).

### Secondary outcome measures

2.8

#### PA—Subjective

2.8.1

Self‐reports of PA are assessed with the International Physical Activity Questionnaire (IPAQ; Craig et al., 2003). We use the short “last 7 days” self‐administered version measuring time spent with four activity levels (vigorous activity, moderate activity, walking, and sitting). The IPAQ correlates moderately with accelerometer data in samples with mental disorders (overall PA: *r* = 0.47; Petzold et al., 2017).

#### Depression—Subjective

2.8.2

Beck Depression Inventory II (Beck, Steer, & Brown, 1996) measures depression subjectively.

#### Anxiety

2.8.3

**Anxiety** symptoms are measured with the Beck Anxiety Inventory (Beck, Epstein, Brown, & Steer, 1988).

#### Other measures

2.8.4

We collect data on sociodemographic variables (sex, age, educational level), former depression episodes and treatments and former or current somatic diseases of the patient. Furthermore, **psychiatric symptoms** are measured using the Symptom‐Checklist‐27 (Hardt & Gerbershagen, 2001) and **health‐related quality of life** with the 12‐Item Short‐Form Health Survey (Ware, Kosinski, & Keller, 1996). As physiological parameters, we collect blood pressure, heart rate, weight, blood glucose, and laboratory values of triglycerides, cholesterol, high density lipoprotein and low density lipoprotein. Because these parameters are not measured routinely in clinics at discharge, only baseline data will be available.

#### Motivational and volitional factors of the MoVo

2.8.5

Besides, we aim to explore the motivational and volitional determinants of PA from the MoVo‐Model.

**Specific self‐efficacy** is measured with six items according to earlier research (Schwarzer, Lippke, & Luszczynska, 2011). There are two items each for action self‐efficacy, maintenance self‐efficacy, and recovery self‐efficacy.

The other constructs are measured according to scales used by Petzold et al. (2017), providing a more detailed description of these measures. The scales contain items about **intention**, **outcome expectancies**, **action planning,** c**oping planning**, **self‐concordance,** and **general self‐efficacy**.

